### Data collection

The study will use a mixed-methods approach with collection of individual-level quantitative, qualitative, provider and participant-cost data, as well as site-level outcome data.

### Individual-level quantitative data collection

The study electronic database for data collection and management has been developed using REDCap (Research Electronic Data Capture) electronic data capture tools [27]. The Zimbabwe MOHCC data collection tools at facilities and CARGs will be used for source data collection including the patient file, the routine electronic patient management system for HIV patients, and routine CARG data collection forms. Trained study-specific nurses will extract source data and capture these with electronic tablet devices following participant CARG or clinic visits. Study nurses will also follow up results of viral-load tests. The data manager will perform regular range checks and missing value checks in the database. On a 3-monthly basis, the study data manager will conduct quality assurance by conducting 100% manual verification checks on a 5% random sample of study participant files of each data capturer’s entries with source data.

### Qualitative data collection

Qualitative data will be collected by trained nurse facilitators at baseline, after 12 months and at the end of the study to understand the acceptability of MMD of ART within CARGs to patients and service providers, as well as to evaluate potential improvements in the quality of service delivery at facilities due to decongestion of facilities. Data collection methods will include focus group discussions (FGD) with study participants and key informant interviews (KII) with facility managers and healthcare workers. One FGD per facility consisting of up to 10 randomly selected CARG participants will be conducted in the vernacular, with 20 FGDs held at each data collection point. Twenty KIIs will be performed at each data collection point. All qualitative data will be recorded, transcribed, translated to English and coded.

### Cost data collection

A micro-costing approach will be used, and a macro-costing approach of fixed costs will be utilized. To ascertain provider costs, both fixed and variable costs will be estimated. Fixed costs will include buildings, equipment, vehicles, CARG supervision and start-up costs, and administration costs. Variable costs for each patient will include outpatient and inpatient care, antiretroviral and non-antiretroviral drug costs, consumables, laboratory tests and components, human resource time per patient, salary cost per patient per service provided and overhead costs including telephone calls and home visits. A resource-use form will be used to collect patient-level costs from a review of clinic records including clinic notes, pharmacy registers, laboratory records and hospital inpatient records. A separate data collection tool will be used to retrospectively collect fixed costs’ information.

Patient-level cost questionnaires will be administered at baseline, 12 months and at 24 months using a pretested data collection tool on a subset of participants (*n* = 1095). Every fifth participant enrolled consecutively per site will be selected for administration of the patient-level cost questionnaires. These costs will include those borne by either the patient or the patient’s relatives to access care. Patient time and accounting for potential loss of income for attending CARG meetings will be incorporated in patient-level costs.

### Site-level data collection

A pre, 12-month and 24-month time-flow survey of patient waiting time over 5 days each will be conducted at each facility using a time-flow recording sheet for each clinic patient. The monthly number of people newly initiated on ART and the monthly number of people who receive provider-initiated HIV testing and counseling per facility will be sourced from routine facility records.

### Data analysis plan

#### Quantitative patient-level data analysis

Descriptive measures of the study population at baseline in each study arm will be conducted using medians and interquartile ranges for continuous variables and proportions for categorical variables, to assess potential imbalances between the arms.

Individual-level outcome analyses will be conducted by intention-to-treat. For the primary outcome of patient retention, risk differences between arms will be estimated using binomial population-averaged generalized estimating equations using an identity link and an exchangeable correlation structure, specifying for clustering by facility. A small cluster size variance correction will be used, and randomization strata will be included in the model as a fixed-effect parameter. If the lower bound of the 95% confidence interval for the risk difference in patient retention of the intervention vs. control arm is greater than the non-inferiority limit of − 3.25%, the intervention will be considered non-inferior to the control. Where there are imbalances between study arms in baseline variables, these will be adjusted for in multivariable analyses.

For the outcome of viral suppression, log-binomial regression with generalized estimating equations will be used to estimate risk ratios between the study arms, specifying for clustering by facility. An exchangeable correlation structure will be used and a small cluster size variance correction applied. Viral-load suppression analyses will be conducted according to: (1) an intention-to-treat principle including all enrolled participants in the arm to which they were originally allocated and irrespective of whether they had available follow-up viral-load results or completed the study and (2) a per-protocol analysis including only patients with available viral-load results. If there are imbalances between study arms in baseline variables, these will be adjusted for in multivariable analyses. Subgroup analyses will include comparing outcomes by strata of urban or rural facility and by gender. A pooled analysis of both intervention arms vs. control will also be performed.

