### Participant eligibility criteria

Participant eligibility will be aligned to those for stable ART patients in routine settings in Zimbabwe [24], and are shown in Table 1.

**Table 1 Tab1:** Inclusion and exclusion criteria for study participants

Inclusion criteria	Exclusion criteria
18 years of age or older	ART toxicity or tolerability issues in the prior 6 months
Confirmed HIV-1 infection based on the Zimbabwe national HIV-testing algorithm	Treatment for an opportunistic infection in the prior month
Received standard first-line ART for 6 months or longer	Receiving alternative first-line or second-line ART regimen
Viral load < 1000 copies/ml at enrollment	Active or suspected opportunistic infection
Weight ≥ 35 kg	Active or suspected tuberculosis
Willing to join a CARG	Comorbidities requiring more frequent visits to the facility than that required by the model of care
Provide informed consent for inclusion in the study	Confirmed pregnancy
	Less than 18 months postpartum

*ART* antiretroviral treatment, *CARG* community antiretroviral treatment-refill group, *HIV* human immunodeficiency virus

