### Sample size estimation

Participant sample size estimates were calculated for the primary outcome of retention in care 12 months after enrollment. Sample size estimates were determined for a non-inferiority test for the difference in two proportions in a cluster-randomized design, using PASS® v.14 software. Participant enrollment numbers are assumed to be equal at each cluster. The probability of participant retention 12 months after study enrollment in the control group is assumed to be 95%, derived from the relative difference in reported retention between 12 and 24 months of ART in Zimbabwe [17]. The probability of retention in the intervention arms after 12 months is also assumed to be 95%. An intracluster correlation coefficient of 0.01 for retention amongst stable ART patients associated with the same healthcare facility is assumed [26]. The non-inferiority margin is prespecified as − 3.25% (risk difference). Assuming *α* = 0.05, power of 85%, and using the one-sided Z-test (unpooled) statistic, 192 participants will be required to be enrolled per facility, with 1920 participants per arm and a total sample size of 5760 enrolled participants. As retention in care is the primary outcome, no adjustment for LTFU is made. Assuming that 75% of those on ART at a healthcare facility will be stable [17] and that 60% of these will consent to be enrolled, to reach the required sample size per facility, selected facilities require at least 430 adults currently receiving ART.

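### Covariates for the multivariable retention and suppression analyses are picked by observed baseline imbalance, with no criterion, instead of from a fixed prognostic list; the harm is modest because the strata-adjusted model is prespecified

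*Protocol article*

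**What the plan says.** All of this is in the protocol article, Data analysis plan, under Quantitative patient-level data analysis, unless another section is named.

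- **Baseline description.** Medians with interquartile ranges, and "proportions for categorical variables, to assess potential imbalances between the arms". No test or threshold is given.
- **Primary model.** Retention is analysed with "binomial population-averaged generalized estimating equations using an identity link and an exchangeable correlation structure, specifying for clustering by facility". A small-sample variance correction is applied, and "randomization strata will be included in the model as a fixed-effect parameter".
- **Decision rule.** This comes next: "If the lower bound of the 95% confidence interval for the risk difference in patient retention of the intervention vs. control arm is greater" than −3.25%, the intervention is declared non-inferior.
- **Further covariates, retention.** Directly after the decision rule: "Where there are imbalances between study arms in baseline variables, these will be adjusted for in multivariable analyses".
- **Further covariates, suppression.** After the log-binomial model: "If there are imbalances between study arms in baseline variables, these will be adjusted for in multivariable analyses". That paragraph names no fixed covariate.
- **Enrolment viral load.** Table 1 under Participant eligibility criteria requires "Viral load < 1000 copies/ml at enrollment", so a result exists for every participant before entry.

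By contrast, Site-level data analysis puts the facility's baseline median waiting time into the waiting-time model unconditionally.

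**The concern.** A covariate is worth adjusting for when it predicts the outcome. Observed imbalance is a different property. A rule based on imbalance brings in variables that have nothing to do with retention and leaves out strong predictors that happen to balance. Because no criterion for imbalance is stated, two analysts with the same baseline table could fit different models.

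The design makes this more than theoretical. Whole facilities are randomised, 10 per arm, so differences in case mix between facilities do not average out as they would over 1,920 independently randomised people. Enrolment follows unblinded allocation. CARG-arm participants come from newly formed groups, while control facilities exclude patients already in CARGs, so recruitment itself may differ between arms.

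The stakes are the reproducibility of the adjusted results, and clarity if the strata-adjusted and multivariable intervals fall on opposite sides of −3.25%. For suppression, the outcome's own baseline measurement may go unused.

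**Working it through.** **1. The plan's own figure.** Inputs from Sample size estimation: retention 95% in both arms, margin 3.25 points, ICC 0.01, 192 per facility, one-sided alpha 0.05; 10 facilities per arm from Study design. Design effect = 1 + 191 × 0.01 = 2.91. SE = √(2 × 0.95 × 0.05 × 2.91 / 1920) = 0.0120. Power = Φ(0.0325/0.0120 − 1.645) = 85.6%, against 85% stated. The figure reproduces and takes no credit for covariates, so nothing here changes the sample size.

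**2. How often imbalance would be seen by chance.** The plan gives no criterion, so two are assumed, with an assumed covariate ICC ρ.

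(a) A 5% test that ignores clustering: P = 2[1 − Φ(1.96/√(1 + 191ρ))].

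| ρ | 0.01 | 0.02 | 0.05 | 0.10 |
|---|---|---|---|---|
| P(flag), one covariate | 25% | 37% | 55% | 66% |

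(b) A standardised difference above 0.1. Its SD is √(2(1 + 191ρ)/1920), which is 0.071 at ρ = 0.02 and 0.105 at ρ = 0.05. One covariate is flagged with probability 16% or 34%. At least one of four independent covariates is flagged with probability 1 − 0.84⁴ ≈ 50% or 1 − 0.66⁴ ≈ 81%.

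**3. Effect on the result.** Two illustrative simulations, with all covariate settings assumed.

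- *Simulation A*: six binary covariates at 40% prevalence, each moving attrition 1.5 to 2.5 points, ρ 0.02 to 0.10, flagged as in (a), cluster-robust variance × 30/25, t on 25 df, 1,500 trials per setting.
- *Simulation B*: two arms, four covariates, ρ 0.02 to 0.05, flagged as in (b), regression of facility means, strata ignored, 4,000 trials per setting.

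| | A | B |
|---|---|---|
| SD of the shift in risk difference (points) | 0.13–0.43 | 0.45–0.69 |
| One-sided error at the margin, no data-chosen covariates | 2.0–3.1% | 2.1–2.9% |
| Same, imbalance-adjusted only | not reported | 2.2–2.8% |
| Same, either interval may count | 2.3–3.5% | 2.7–3.7% |
| Verdicts disagree, no true difference | not reported | 7.5–13% |

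Monte Carlo SE near 2.5% is √(0.025 × 0.975/1500) = 0.40 points in A and 0.25 in B, so small differences between rows are partly noise.

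**4. Precision from a fixed list.** In A, fitting all six covariates made the SE 1% to 7% smaller. In B, fitting all four lowered power to 61–65%, from 72–73% without covariates; the imbalance rule gave 65–69%. B regresses only 20 facility means, so each covariate uses one of 18 residual degrees of freedom. The planned GEE uses individual data from 30 facilities and should suffer less. B is still a reason to keep the list short.

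**5. Enrolment viral load and suppression.** Assume 10% to 15% have detectable viraemia below 1000 copies/ml and fail 15 to 20 points more often. No suppression rate is given in the article, so two are assumed.

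- 95% suppressed: 0.09 × 0.15²/0.0475 = 4.3%, to 0.1275 × 0.20²/0.0475 = 10.7% of individual variance.
- 90% suppressed: the same numerators over 0.09 give 2.3% to 5.7%.

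If ICC is 0.01 here too, the within-facility share of arm-level variance is 0.99/2.91 = 34%. If baseline viral load is similar across facilities, the 95% case reduces the SE by 1 − √(1 − 0.34 × 0.043) = 0.7%, to 1 − √(1 − 0.34 × 0.107) = 1.8%.

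**The case against.** A reader might infer that the non-inferiority decision itself depends on covariates chosen after looking at the data. The article does not support that. The decision rule directly follows the fully specified strata-adjusted model, and the imbalance sentence comes afterwards and speaks of multivariable analyses. The trigger is the baseline table, not outcomes. The second interval arises only if imbalance is found. This objection stands, and it confines the point to the supportive analyses. What remains is that no sentence says which interval governs if the two disagree.

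The numbers also show little harm. The imbalance-adjusted analysis alone holds its error near 2.5%, and the worst case, in which either interval may count, is about 3.5% to 3.7%. The flag probabilities rest on criteria and ICCs that the article does not state. Enrolment viral load is truncated at 1000 copies/ml, and suppression is secondary. All of this stands and sets the severity.

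It can also be said that covariate lists belong in a statistical analysis plan. That would answer an omission. Here the article states a selection rule, twice, and the rule is the weaker one.

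Finally, differential recruitment after allocation is a sound reason to want to respond to an unforeseen imbalance. That stands too, and the fix leaves room for it.

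**Conclusion.** The point holds in a limited form. Selecting covariates by observed imbalance, without a criterion, makes the multivariable retention and suppression results depend on the baseline data seen, and leaves enrolment viral load out of the suppression model unless it looks imbalanced. With 10 facilities per arm the rule will probably be triggered, though the probability depends on the assumed criterion and ICC.

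The consequences are modest: adjusted estimates that shift by a few tenths of a percentage point (SD 0.13 to 0.69 across the assumed settings, against a design SE of 1.20), possible ambiguity if the two intervals disagree, and probably no more than a few percent of the SE in lost precision. Material error inflation is not shown. The main gain from a fixed list is a reproducible analysis; a power gain is not assured. The choice of link function is a separate question and is not part of this point.

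**What to change.** 1. Add a clause to the decision rule: non-inferiority is judged on the risk difference from the strata-adjusted GEE.
2. Replace both imbalance sentences with a short fixed list of prognostic covariates, for example age, sex, time on ART and enrolment viral load category. Use it in one supportive retention model whatever the observed balance.
3. Always include enrolment viral load category in the suppression model.
4. Label any further adjustment for an unforeseen baseline imbalance as an exploratory sensitivity analysis.

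The cost is a wording change; the sample size is untouched. Eligibility screening already checks age, duration of ART and viral load, and gender is a planned subgroup factor. The article shows only the eligibility thresholds, so the sponsor should confirm that the actual values are held as analysis variables. The downside is small: the precision gain will be slight, and a long list would use up degrees of freedom with 30 facilities, so it should stay short.

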### Site-level data analysis

Summary measures of patient waiting time for each facility at each assessment point will be calculated. The difference in waiting time at 12 and 24 months vs. the baseline survey will be calculated within each arm, and differences in waiting time will be compared between arms. In addition, between-arm comparisons of 12- and 24-month waiting times will be conducted with a two-level, mixed-effects linear model including the median baseline facility waiting time as a fixed covariate and specifying facility as a random effect. A secondary analysis will involve inclusion of other site-specific potential confounding variables as fixed effects in the model.

Plots will be drawn of the monthly numbers of patients newly initiated on ART and monthly numbers who receive provider-initiated HIV counseling and testing per site for each arm to assess trends during the study period, and multilevel, mixed-effects linear regression will be used to compare arms. A secondary analysis will include adjustment for potential site-specific confounding.

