## Discussion

No large-scale trials have been conducted investigating patient-level outcomes and health system costs of extended ART-dispensing intervals for patients within community-based groups in sub-Saharan Africa. The rationale for this study is to provide evidence regarding the effectiveness and cost-effectiveness of extended dispensing intervals for ART patients within CARGs, and whether these are suitable strategies that can be implemented on a larger scale to help overburdened health facilities with the large numbers of patients and reduce the burden and cost to patients of frequent clinic visits. Study results are expected to inform health policy both in Zimbabwe and in the entire sub-Saharan African region.

The trial is implemented through a collaboration between Kheth’Impilo AIDS Free Living, EQUIP Innovation for Health, the Organization for Public Health Interventions and Development, FHI 360, the Zimbabwe AIDS Prevention Project Trust and the Zimbabwe MOHCC. Implementation challenges include large distances between facilities, limited access to routine viral-load testing within the country and limited Internet connectivity in rural areas.

The strengths of the study include that a variety of outcome data will be analyzed including clinical effectiveness data, provider- and patient-cost data, qualitative data and site-level impact data. Routine ART facilities from both urban and rural areas are included in a pragmatic design, which is expected to allow study results to be generalizable to other sub-Saharan African settings. The study limitations include that participants in the 3MF arm may not complete 24 months’ follow-up in this arm as, according to MOHCC operational recommendations, they will be provided the option of forming CARGs after 12 months of study participation. The sample size in the 3MF arm may thus be reduced at the 24 months’ outcomes assessment, thus comparisons may have reduced power. However, this will not impact the primary outcome ascertainment of patient retention 12 months after enrollment. Participant viral-loads results may not be complete due to limitations in the availability of viral-load testing in the country. Viral suppression is thus a secondary outcome. It will also not be possible for participants or providers to be blinded as to the study group allocation.

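### The randomisation strata are in the retention model but not in the stated viral-suppression, waiting-time or monthly-count models, and the suppression analysis does not fix how untested participants count

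*Protocol article*

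**What the plan says.** Under Quantitative patient-level data analysis, the retention model is a binomial GEE with facility clustering, exchangeable correlation and a small-sample variance correction, and "randomization strata will be included in the model as a fixed-effect parameter". The next paragraph covers viral suppression: "log-binomial regression with generalized estimating equations will be used to estimate risk ratios between the study arms, specifying for clustering by facility". It continues: "An exchangeable correlation structure will be used and a small cluster size variance correction applied". Strata are not mentioned there. The only covariate adjustment named is for baseline variables found to be imbalanced, and a subgroup analysis by urban or rural facility is planned.

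Under Site-level data analysis, waiting time is modelled with the facility's median baseline waiting time as a covariate and facility as a random effect. For monthly ART initiations and HIV tests, "multilevel, mixed-effects linear regression will be used to compare arms". Neither model names the strata, and the count model names no pre-trial level. Secondary analyses with site-specific confounders are planned for both.

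Suppression is to be analysed in two sets: all enrolled participants, "irrespective of whether they had available follow-up viral-load results or completed the study", and "a per-protocol analysis including only patients with available viral-load results". Neither is named as the lead. The Definitions section gives the threshold (below 1000 copies/ml) but no rule for a missing result. The Discussion warns: "Participant viral-loads results may not be complete due to limitations in the availability of viral-load testing in the country". It adds: "Viral suppression is thus a secondary outcome".

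**The concern.** Stratified allocation removes stratum differences from the between-arm comparison, but the reported standard error reflects this only if the model includes the strata. Otherwise stratum differences stay in the residual between-facility variance and the interval is wider than it should be. The rule of adjusting for imbalanced baseline variables would not bring the strata in, because they are balanced by design. With 10 facilities per arm, the lost precision matters for secondary outcomes that are meant to inform policy.

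The missing-result question is separate. A participant without a viral load cannot meet the threshold definition, so the all-enrolled analysis most naturally scores that participant as not suppressed. The stated reason for missing results is test supply, not treatment failure. Under Description of interventions, control participants collect their own ART at the facility every 3 months, while CARG members all attend only at 12 and 24 months. Chances to obtain a delayed test could therefore differ by arm, in either direction. The tested-only analysis has the opposite limitation: it leaves out deaths and losses without a result. It is a complete-case set and does not depend on adherence to the allocated model, so per-protocol is the wrong label.

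**Working it through.** **The plan's own figure.** The article gives no figure for suppression, so the design inputs come from Sample size estimation: retention 95% in both groups, margin 3.25 points, one-sided alpha 0.05, power 85%, ICC 0.01, 192 per facility, 10 facilities per arm. An individually randomised design needs 647 per arm. The design effect is 1 + 191 × 0.01 = 2.91, and 647 × 2.91 ≈ 1883, against 1920 stated. Power at 1920 is 85.6%. The inputs reproduce, and the ICC and cluster size are used below. The ICC is stated for retention; carrying it over to suppression is an assumption.

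**Strata, by formula.** Let r be the share of between-facility variance explained by strata (assumed 0.3–0.5).
- Purely facility-level outcome: interval inflation is 1/√(1 − r), which is 1.20 at r = 0.3 and 1.41 at r = 0.5.
- Individual-level outcome: only part of the variance of a facility proportion lies between facilities, namely 0.01/(0.01 + 0.99/192) = 0.66. Inflation is 1/√(1 − 0.66r), which is 1.12 at r = 0.3 and 1.22 at r = 0.5.

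**Strata, by simulation.** Thirty facilities (6 urban, 12 rural hospitals, 12 rural clinics), 192 participants each, no true arm effect, 4000 runs per scenario. A linear analysis of facility proportions stands in for the GEE. Stratum proportions and facility SDs are assumptions.

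| Stratum proportions | Facility SD | Mean SE without / with strata | Two-sided type I error without / with |
|---|---|---|---|
| 93/93/93% | 2 points | 0.0120 / 0.0120 | 5.0% / 4.9% |
| 96/93/90% | 2 points | 0.0160 / 0.0122 | 0.9% / 4.6% |
| 90/85/80% | 5 points | 0.0302 / 0.0248 | 1.7% / 4.7% |

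The point estimate was the same with and without strata in every run. The second row shows 31% inflation (0.0160/0.0122) because its r lies above the 0.3–0.5 range. The weighted mean is 0.924 and the variance between strata is 0.2 × 0.036² + 0.4 × 0.006² + 0.4 × 0.024² = 0.000504, so r = 0.000504/(0.000504 + 0.02²) = 0.56. The third row gives 0.0302/0.0248 = 1.22.

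**Test coverage.** If untested counts as not suppressed, the risk ratio is (s₁t₁)/(s₀t₀), where s is true suppression and t the share tested (1 = intervention, 0 = control). With s = 95% in both arms (an assumption), s cancels:
- 90% vs 90%, or 70% vs 70%: 1.00
- 80% vs 90%: 0.89
- 90% vs 80%: 1.13

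The article gives no coverage rate, so these pairs only show the range. Coverage can also differ by chance: with a facility SD of 10 points (an assumption), the SE of the arm difference in coverage is 0.10 × √(2/10) = 4.5 points. A cluster-adjusted interval allows for chance differences of this kind, but not for a systematic one due to the model of care.

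**The case against.** Much of this rests on silence in a condensed article, and a full analysis plan may name the strata for every model. That is fair, but the suppression paragraph repeats the clustering, correlation structure and small-sample correction from the paragraph before and leaves out only the strata, so an analyst following the text would leave them out too.

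The omission is harmless if strata do not differ and conservative if they do. That stands. A reader might infer that the omission adds noise to the estimate; with 2/4/4 in every arm it does not, and only the reported precision suffers. Nor does the 20–41% range apply to suppression, since it treats all variance as between-facility.

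For the site-level models, baseline waiting time may already absorb part of the stratum difference. The count outcomes are trends, for which a facility random effect takes up much of the level. The planned secondary adjustment could also include facility type. All of this weakens the point there.

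On missing results, a reader might infer that the suppression analysis simply measures test access. The article does not support that. The coding of untested participants is not stated, and including everyone is also compatible with imputation. A tested-only analysis is planned as well. The risk ratio moves only if coverage differs between arms, and the shortage is described as national. Whether imputation should lead is a matter of judgement.

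**Conclusion.** The strata point holds as a loss of reported precision, not as bias. Intervals are about 12–22% too wide for suppression, and up to 20–41% for purely facility-level outcomes, if strata explain 30–50% of between-facility variance. There is no loss if strata do not differ. The 20–41% is an upper range for waiting time and counts, given the baseline covariate and the focus on trends.

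The missing-result point is secondary and conditional. It depends on scoring untested participants as not suppressed and on coverage differing between arms; the article settles neither. What the article does fix badly is that two analyses which can disagree have no stated lead, and one carries the wrong label. The retention analysis at 12 months already includes the strata and does not use viral loads, so the primary conclusion is unaffected.

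**What to change.** 1. Add the three strata as fixed effects to the suppression, waiting-time and monthly-count models. This uses two further degrees of freedom (27 to 25 in a facility-level analysis with three arms).
2. Add each facility's pre-trial monthly count to the count models, from the routine records already named under Site-level data collection. The cost is some extra extraction.
3. State how a missing viral load is handled: count death and LTFU as not suppressed, and treat retained-but-untested participants separately, for example by multiple imputation using arm, facility, stratum and baseline covariates as an added analysis. This relies on a missing-at-random assumption and modest programming.
4. Name the lead suppression analysis, keep the others as sensitivity analyses, and relabel the tested-only set as available-case.
5. Report test coverage by arm at 12 and 24 months.
6. State which suppression analysis supplies the denominator for provider cost per participant retained with suppression.
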